### Sample size calculation

The sample size was determined based on a (one-proportion) power calculation assuming a proportion of 45% of all patients with pT1 CC to be cured with local resection (proportion low-risk T1 CC, R0 resection). For the sample size calculation, we used a desired width of a two-sided 95% confidence interval of 0.2. This calculation resulted in a sample size of 96 patients with pT1 CC. As we estimate to exclude 15% of the patients because of a pT2 CC, 10% due to benign histology and an overall technical failure in 10% [22], a total sample size of 143 patients is calculated. We will perform a mid-term evaluation at half the target number of inclusions. If the proportion of patients with pT1 CC is lower than 60% at that stage, the inclusion will be temporarily suspended and the principal investigators will critically assess the current mode of inclusion.

### Data analysis

Data on demographic and baseline characteristics will be summarized for continuous variables, in case of normal distribution by mean and standard deviation (SD), and in case of non-normal distribution by median and (interquartile) range. Discrete variables and categorical data will be presented as proportions of patients (percentages). All baseline characteristics and differences in secondary outcomes, such as morbidity and postoperative QoL, will be compared between patients that only received CAL-WR versus patients that received also additional oncologic resection, using the Student’s T-test (in case of normally-distributed continuous data) or the Mann–Whitney U test (in case of non-parametrical continuous data). Normality will be verified using the Kolmogorov–Smirnov test. A (two-sided) *p*-value < 0.05 will be considered significant. The primary endpoint will be described as the proportion (percentage with 95% confidence interval) of patients with pT1 CC where only local resection with CAL-WR appeared to be curative and thereby oncologic resection was prevented. The 5-year overall survival and disease free survival will be assessed using a Kaplan–Meier analysis*.* The 30-day postoperative morbidity and mortality will described as proportions (percentages). Data analysis will be performed by using the Statistical Program for the Social Sciences (SPSS) version 28.0 (IBM. Corp, Armonk, New York, USA).

The cost analysis will be conducted from a hospital’s perspective. Total procedure-related cost of CAL-WR will be calculated in Euro. Healthcare costs will be calculated by multiplying used healthcare services by the appropriated unit cost prices. Bottom-up micro costing will be applied. For all other healthcare services reference prices, will be used where available. Costs will be discounted to correct for inflation. Eventually, the cost efficiency of our strategy will be calculated, considering also the number of patients that will need two operations i.e. patients with high risk T1 or ≥ T2.

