### Objectives

The primary objective of this study is to determine the proportion of patients with pT1 CC for whom CAL-WR was shown to be formerly a curative treatment (i.e. low-risk T1 CC, R0) and in whom an (additional) segmental resection could thus be prevented. Secondary objectives are to evaluate CAL-WR’s technical success and R0 resection rate for T1 CC, procedure-related morbidity and mortality, the 5-year overall and disease free survival, 3-year metastases free survival, its costs, and the impact on QoL.

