### Follow-up

After CAL-WR and subsequent histological examination, 3 groups will be formed i.e. (1) benign pathology, (2) low risk T1 CC (i.e. carcinomas with absence of histological high risk features for lymph node metastasis), and (3) high risk T1 CC (i.e. carcinomas with histological high risk features for lymph node metastasis) or accidentally found ≥ pT2 (Fig. 3). All patients diagnosed with a benign colonic polyp, will receive a follow-up colonoscopy after 1 year to evaluate local recurrence rate. Patients diagnosed with low risk T1 CC will undergo colonoscopy 12 and 48 months after curative radical (R0) resection, according to the current national guideline. In case patients are diagnosed with an incomplete resected low risk 1 CC, high risk T1 CC or ≥ pT2, completion surgery is advised. All patients with an indication for completion surgery will be staged with chest and abdomen imaging by computer tomography (CT) to rule out potential synchronous metastasis and will subsequently be discussed in the multidisciplinary team meeting. If completion surgery is considered to be beneficial, it needs to be performed within six weeks after initial CAL-WR in order to guarantee the patients’ oncological outcome [30]. In case of high complication risks and/or based on the patients’ choice, there can be refrained from a complementary resection and give preference to intensive follow-up. The impact of CAL-WR on QoL will be evaluated in all patients, also those that undergo completion surgery, using three questionnaires (EQ-5D-5L, QLQ CR29 and CWS). The questionnaires will be performed at baseline, at 3 and 36 months after the procedure. Participation in the national Prospectief Landelijk CRC cohort (PLCRC) is preferable for the questionnaires [31].

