#### Secondary endpoints

Effectiveness (technical success and macroscopic- and microscopic radical resection)30-day postoperative morbidity and mortality rate. Complications will be assessed according to the Clavien-Dindo classification. Clavien-Dindo grade I and II complications will be classified as minor and grade III-V complications as major.3-year metastasis free survival defined as the development of metastasis outside the area of the intended surgery (intensive surveillance), or after completion surgery.5-year overall survival and disease free survival (disease free survival is defined as the time between surgery until local cancer recurrence or detection of distant metastasis)Total procedure related and postoperative costs (‘in-hospital’ costs between the primary day of surgery until 30-days after discharge)Postoperative quality of life

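### The QoL objective is the impact of CAL-WR in all patients, but the only stated analysis compares postoperative scores between two non-randomised groups, without change from baseline or baseline adjustment

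*Protocol article*

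**What the plan says.** All references are to the protocol article.

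- **Objectives** ends its list of secondary objectives with "3-year metastases free survival, its costs, and the impact on QoL".
- **Follow-up** gives the population: "The impact of CAL-WR on QoL will be evaluated in all patients, also those that undergo completion surgery, using three questionnaires". The instruments named there are CWS, EQ-5D-5L and QLQ CR29. The same section gives the timing: "The questionnaires will be performed at baseline, at 3 and 36 months after the procedure".
- **Secondary endpoints** names the endpoint only as "Postoperative quality of life".
- **Data analysis** states the comparison: "differences in secondary outcomes, such as morbidity and postoperative QoL, will be compared". The two groups are those treated by CAL-WR alone and those who went on to a further oncologic resection. The methods are given as "using the Student’s T-test (in case of normally-distributed continuous data) or the Mann–Whitney U test", the latter for data that are not normally distributed. The significance rule is: "A (two-sided) *p*-value < 0.05 will be considered significant".

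No section mentions change from baseline, a paired or repeated-measures analysis of QoL, or adjustment for baseline QoL.

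**The concern.** There are two separate faults.

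**The analysis does not match the objective.** The study has one arm. The impact of a procedure on QoL in all its patients is, at the least, how their scores move from before it to after it. A comparison of two subgroups on their postoperative level answers a different question, namely how the subgroups differ afterwards. Both groups could lose, keep or gain QoL and the contrast would be the same.

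**The contrast is open to baseline differences.** Follow-up forms the groups after CAL-WR, by histology and margin status. It also allows patients to forgo completion surgery because of high complication risk or their own preference. Frailer patients may therefore remain in the CAL-WR-only group, which is one route to unequal QoL at baseline. Neither named test can take a baseline covariate.

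At stake is a named secondary objective. It could end with a p-value judged at 0.05 for a contrast that is not the impact of CAL-WR and may partly reflect who was in each group.

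**Working it through.** **1. The plan's own figures.** The document gives no effect size, standard deviation (SD) or power for QoL. Its sample size rests on the primary endpoint and reproduces:

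- pT1 patients: 1.96² × 0.45 × 0.55 / 0.10² = 95.1, rounded up to 96.
- Total: 96 / (0.75 × 0.90) = 142.2, rounded up to 143.

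Nothing below changes these figures.

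**2. What the stated contrast estimates.** Let d be the baseline gap between the groups and rho the correlation between baseline and follow-up scores, with equal SDs at both times. If the additional resection has no effect and baseline QoL is the only source of difference:

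- unadjusted postoperative comparison: expected difference = rho × d
- comparison of change scores: expected difference = (rho − 1) × d
- comparison with baseline as covariate (ANCOVA): expected difference = 0

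**3. Illustrative size.** All values of rho and d are assumptions. For group sizes I take 45% and 55% of 96, that is 43 and 53. Actual groups may differ, because benign and pT2 cases and patients who decline completion surgery also fall into them.

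Standard error of the difference = √(1/43 + 1/53) = 0.205 SD. With b = rho × d, the two-sided rejection rate at 0.05 is 1 − Φ(1.96 − b/0.205) + Φ(−1.96 − b/0.205).

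| rho | d (SD) | Bias, postoperative scores | Rejection rate | Bias, change scores |
|---|---|---|---|---|
| 0.3 | 0.2 | 0.06 | 6% | −0.14 |
| 0.5 | 0 | 0 | 5% | 0 |
| 0.5 | 0.3 | 0.15 | 11% | −0.15 |
| 0.5 | 0.5 | 0.25 | 23% | −0.25 |
| 0.7 | 0.5 | 0.35 | 40% | −0.15 |

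The row with d = 0 shows that the bias vanishes if the groups start level.

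**4. Precision.** ANCOVA residual variance = (1 − rho²) × postoperative variance.

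- rho 0.5: 1 − 0.25 = 0.75, a cut of 25%, worth 1/0.75 = 1.3 times the sample.
- rho 0.7: 1 − 0.49 = 0.51, a cut of 49%, worth 1/0.51 = 2.0 times the sample.

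The difference detectable with 80% power is (1.960 + 0.842) × 0.205 = 0.575 SD unadjusted. Multiplying by √(1 − rho²) gives 0.498 SD at rho 0.5 and 0.411 SD at rho 0.7. This gain does not depend on a baseline gap.

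**The case against.** **This is detail for the analysis plan.** A journal article condenses the protocol, and one generic sentence covers all secondary outcomes, with QoL only as an example. Covariates and repeated-measures models are often specified elsewhere. This would answer a complaint about silence. The article is not silent, however: it names the variable, the groups, the tests and the significance level, and these do not fit the objective it sets.

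**Baseline QoL is not excluded.** This is correct. A reader might infer that the study will never use the baseline forms, and the document does not support that. Data analysis compares all baseline characteristics between the same groups, which may include QoL, and Follow-up promises an evaluation in all patients without giving its method. What can be said is narrower: no stated QoL outcome analysis uses the baseline score, and a baseline comparison neither adjusts the outcome nor estimates change.

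**No bias is shown.** This is also correct. A reader might infer that the contrast is known to be biased. The groups form mainly on histology and margins found after CAL-WR, which are unknown when the baseline form is completed, so the gap could be small. The opt-out is a plausible route to imbalance, but its size is unknown.

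**Missing forms.** A reader might add that patients with a missing follow-up form drop out of that time point. Any available-case comparison does this, and the article states no missing-data rule, so it is not an error in the text.

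**Adjustment does not make the contrast causal.** This stands. Tumour stage, fitness and patient choice still differ between the groups.

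**Conclusion.** The point holds as a mismatch between objective and stated method. The QoL objective concerns impact in all patients and a baseline questionnaire is collected, yet the stated analysis is an unadjusted comparison of postoperative scores between two groups formed by pathology, risk and choice. It does not estimate change after CAL-WR, and it lets through whatever baseline gap exists.

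The mismatch follows from the text without any assumption. The magnitude does not: bias of 0.06 to 0.35 SD and rejection rates of 6% to 40% arise only under assumed gaps of 0.2 to 0.5 SD and correlations of 0.3 to 0.7. The variance reduction of 25% to 49% rests on an assumed correlation of 0.5 to 0.7.

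This is a secondary endpoint without its own power calculation. The primary endpoint, the 96 and 143 patients and the mid-term evaluation are untouched.

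**What to change.** 1. Make within-patient change the main QoL result: mean change from baseline with a 95% confidence interval at 3 and 36 months for each score, overall and per group.
2. Base any contrast between CAL-WR alone and CAL-WR plus resection on a model with baseline QoL as a covariate. This can be ANCOVA at each time point, or a mixed model of the 3- and 36-month scores with baseline as covariate.
3. Do not treat a mixed model with baseline as one of the responses as equivalent. With unequal baselines it can yield a change-score contrast, which carries a bias of (rho − 1) × d. For the same reason, do not subtract the two groups' mean changes to obtain the contrast.
4. Label the group contrast descriptive, since confounding by stage, fitness and patient choice remains.
5. Reword the endpoint so that it names change from baseline as well as the postoperative level.

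The cost is wording in the analysis section or the analysis plan, best settled before the QoL data are analysed. It needs no further patients, visits or questionnaires, and the software named in the article can fit these models.

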#### Participating surgeons

All participating surgeons must be experienced in laparoscopic colorectal surgery. Aiming to further standardize the procedure, all participating surgeons must have attended an e-learning concerning the technique and the possible pitfalls of the technique. However, the majority of the surgeons is already familiar with CAL-WR by participating in our previous trial [22]. Patients will be informed by the surgeon about the possibility of conversion into an laparoscopic or open major oncologic resection if perioperative CAL-WR is not feasible.

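### The secondary comparison groups patients by surgery received, so its CAL-WR-only group mixes benign, cured and unoperated higher-risk patients, and converted patients fit neither group

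*Protocol article*

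**What the plan says.** The Data analysis section names one between-group comparison. Its content is "All baseline characteristics and differences in secondary outcomes, such as morbidity and postoperative QoL", and these "will be compared between patients that only received CAL-WR versus patients that received also additional oncologic resection". The tests named for it are Student's t-test and the Mann-Whitney U test, and "A (two-sided) *p*-value < 0.05 will be considered significant". The comparison is not restricted to pT1, and no stratification or adjustment by pathology is stated.

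The Follow-up section determines who falls into which group. After CAL-WR, "3 groups will be formed i.e. (1) benign pathology, (2) low risk T1 CC", and a third group of high-risk T1 or at least pT2. For an incompletely resected low-risk T1, "high risk T1 CC or ≥ pT2, completion surgery is advised". Where complication risk is high, or the patient so chooses, "there can be refrained from a complementary resection and give preference to intensive follow-up". The same section adds: "The impact of CAL-WR on QoL will be evaluated in all patients, also those that undergo completion surgery".

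The Participating surgeons section says that patients are told of the "possibility of conversion into an laparoscopic or open major oncologic resection if perioperative CAL-WR is not feasible". The Sample size calculation section plans for 10% technical failure, 15% pT2, 10% benign histology and 45% curative local resection among pT1.

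**The concern.** Membership of either group is settled after the index operation, by whether a second operation took place. That depends on pathology, on margin status, on fitness for major surgery and on patient preference. The CAL-WR-only group therefore joins three kinds of patient with different prognosis and frailty: those who never had cancer, those cured by the wedge resection, and those who had a reason for completion surgery but did not undergo it. The other group has had two operations by definition. A p-value below 0.05 for morbidity or quality of life in this contrast cannot be attributed to organ preservation, yet it would be the only between-group result that the study offers.

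A patient converted to an oncologic resection during the index procedure did not receive CAL-WR alone and did not receive a resection in addition to it. No rule in the article assigns such a patient.

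Morbidity is listed among the compared outcomes and is described elsewhere in the same section as a proportion, but the tests attached to the comparison are for continuous data.

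**Working it through.** **Inputs** (Sample size calculation section): curative proportion 0.45 among pT1; total 95% CI width 0.2; 96 pT1 patients; technical failure 10%; pT2 15%; benign 10%; total 143. The share of indicated patients who forgo completion surgery is not given and is varied below as an assumption.

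**Step 1. Reproduce the plan's figures.**
- pT1 patients: n = 1.96² × 0.45 × 0.55 / 0.1² = 95.08, rounded up to 96.
- Total: 96 / (0.75 × 0.90) = 142.2, rounded up to 143.

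Both figures reproduce. Other ways of combining the three losses do not give 143: 96/0.65 gives 148, 96/(0.85 × 0.90 × 0.90) gives 140, and 96 × 1.35 gives 130. The plan thus takes technical failure off first and applies the pathology rates to completed procedures.

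**Step 2. Expected composition at N = 143.**
- Technical failures: 0.10 × 143 = 14.3
- Completed CAL-WR: 143 − 14.3 = 128.7
- Benign: 0.10 × 128.7 = 12.9
- pT2: 0.15 × 128.7 = 19.3
- pT1: 0.75 × 128.7 = 96.5
- Low-risk R0 T1: 0.45 × 96.5 = 43.4
- pT1 with an indication for completion surgery: 96.5 − 43.4 = 53.1
- All with an indication: 53.1 + 19.3 = 72.4, of whom 19.3/72.4 = 27% are pT2

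**Step 3. Content of the CAL-WR-only group.** With a share q of indicated patients forgoing completion surgery, taken as equal for pT1 and pT2, the size is 12.9 + 43.4 + 72.4q.

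| q (assumed) | CAL-WR only | Benign | Low-risk R0 T1 | Indicated, not operated | Second group |
|---|---|---|---|---|---|
| 0% | 56.3 | 23% | 77% | 0 | 72.4 |
| 10% | 63.5 | 20% | 68% | 7.2 (11%) | 65.2 |
| 20% | 70.8 | 18% | 61% | 14.5 (20%) | 57.9 |
| 30% | 78.0 | 16% | 56% | 21.7 (28%) | 50.7 |

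The first row needs no assumption beyond the plan's own rates, apart from everyone with an indication being operated on.

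**Step 4. Converted patients.** The 14.3 technical failures are an upper figure for conversions. The article says that conversion may occur, not that every failure leads to one.

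**Step 5. Would removing benign and pT2 patients cure it?** Suppose the Sample size section's exclusions were meant for every analysis. The CAL-WR-only group would then be 43.4 + 53.1q. At q = 10% this is 48.7, with 5.3 (11%) indicated but not operated. At q = 30% it is 59.4, with 15.9 (27%). The selection on fitness and choice would remain.

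**The case against.** The strongest case for leaving the text alone is that this is a single-arm study whose primary endpoint is one proportion with a confidence interval, and that the authors claim no causal effect from the comparison. One versus two operations is a legitimate descriptive contrast for a two-step strategy, and the article wants quality of life in all patients and the cost of two operations counted. That is fair and limits the weight of the point. It does not explain why the contrast carries a significance test, or why benign and unoperated higher-risk patients should sit with the cured ones.

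Several stronger readings are tempting, and the article does not support them.
- A reader might infer that every secondary outcome is to be tested. The word 'all' most directly governs baseline characteristics; for survival only Kaplan-Meier analysis is named, without a group test.
- A reader might infer that the three Follow-up groups are a ready-made clean alternative. They are not. The low-risk group is defined by absence of risk features and so can include R1 and Rx patients, and the third group merges high-risk T1 with pT2 or beyond.
- A reader might infer that unassigned conversions hide morbidity. The article also reports 30-day morbidity and mortality as proportions without restriction to the two groups, and technical success is its own endpoint. Nothing in it says that converted patients have the most major morbidity.
- The authors may have meant to count conversions with the resections, but the text does not say so.

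It can also be said that an article may leave the test for proportions to the full protocol. Silence alone would be no finding. Here, however, the sentence attaches morbidity to two continuous-data tests, which is a misfit in what is stated, though a minor one.

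Finally, a contrast of low-risk R0 patients with those who had completion surgery is still defined after treatment and still confounded. That objection stands, so such a contrast can only be descriptive.

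**Conclusion.** The point holds for this secondary comparison and should be corrected before analysis. As worded, its first group is heterogeneous by construction, and patients converted at the index operation have no place in it or in the second group. The minimum size of the problem, on the plan's own rates, is about 13 benign patients among 56 (23%). The range of 56-68% for low-risk R0 T1 rests on an assumed 10-30% of indicated patients forgoing completion surgery, a rate that the article does not give. The figure of about 14 conversions is a ceiling. Observed differences in morbidity or quality of life would partly reflect pathology and fitness for surgery. The reading that benign and pT2 patients are removed from every analysis is unlikely, given the unrestricted Data analysis wording and the all-patient quality-of-life evaluation, and it would not resolve the matter.

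The primary proportion, the sample size of 143 and the overall 30-day morbidity and mortality proportions are unaffected.

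**What to change.** In the Data analysis section, replace the two-group test with descriptive reporting of secondary outcomes, with 95% confidence intervals, in five groups:
1. low-risk T1 with R0 margins;
2. completion surgery indicated and performed;
3. completion surgery indicated but not performed;
4. benign histology;
5. technical failure or conversion at the index operation.

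If one two-group contrast is kept, define it as group 1 versus group 2, state that it is descriptive and non-causal, and compare morbidity with Fisher's exact test instead of the t-test or Mann-Whitney test.

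The cost is wording. Histology and margin status are in the Histopathological examination section, technical success is a secondary endpoint, and receipt of a second operation is already needed for the comparison as planned. The downside is small groups with wide intervals: about 13 benign patients, at most about 14 failures, and about 7 to 22 indicated but unoperated patients at the assumed rates. With 0 events in 13 patients, for example, the exact 95% upper limit is 1 − 0.025^(1/13), about 25%.

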## Abstract

**Background:**

The sole presence of deep submucosal invasion is shown to be associated with a limited risk of lymph node metastasis. This justifies a local excision of suspected deep submucosal invasive colon carcinomas (T1 CCs) as a first step treatment strategy. Recently Colonoscopy-Assisted Laparoscopic Wedge Resection (CAL-WR) has been shown to be able to resect pT1 CRCs with a high R0 resection rate, but the long term outcomes are lacking. The aim of this study is to evaluate the safety, effectiveness and long-term oncological outcomes of CAL-WR as primary treatment for patients with suspected superficial and also deeply-invasive T1 CCs.

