## Methods

In this prospective multicenter clinical trial, patients with suspected T1 CC (after assessment by an expert panel) will receive CAL-WR as initial treatment in order to prevent unnecessary segmental resections for low risk T1 CC.

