### Outcomes

#### Primary endpoint

Proportion of patients with pT1 colon carcinoma for whom CAL-WR was shown to be a curative treatment (i.e. low-risk T1 CC, R0) and in whom an (additional) segmental resection could thus be prevented (percentage of patients).

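### The aim concerns suspected T1 cancer, but the primary proportion is restricted to pT1, known only after surgery; proportions over all patients started on CAL-WR should be co-reported

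*Protocol article*

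**What the plan says.** The Abstract (Background) sets the aim as evaluating "CAL-WR as primary treatment for patients with suspected superficial and also deeply-invasive T1 CCs", and the last paragraph of the Background section says much the same. The opening of Methods states that patients with suspected T1, after panel assessment, "will receive CAL-WR as initial treatment in order to prevent unnecessary segmental resections for low risk T1 CC". Under Study design and Expert panel, inclusion rests on endoscopic suspicion, the local multidisciplinary meeting, technical feasibility and patient preference.

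The primary endpoint is "Proportion of patients with pT1 colon carcinoma for whom CAL-WR was shown to be a curative treatment", defined as low-risk with an R0 margin. Objectives uses the same denominator, and so does Data analysis: "The primary endpoint will be described as the proportion (percentage with 95% confidence interval) of patients with pT1 CC". Histology comes later. Under Follow-up: "After CAL-WR and subsequent histological examination, 3 groups will be formed".

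The Sample size calculation starts by "assuming a proportion of 45% of all patients with pT1 CC to be cured with local resection" and then allows for patients who leave the denominator: "As we estimate to exclude 15% of the patients because of a pT2 CC, 10% due to benign histology", plus 10% technical failure. The Discussion accepts that some lesions other than T1 will be included despite the panel.

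Second operations appear in two places. Follow-up advises completion surgery for incompletely resected low-risk T1, for high-risk T1 and for pT2 or higher. The cost paragraph of Data analysis takes into account how many patients need two operations, described there as high-risk T1 or T2 and above.

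**The concern.** When CAL-WR is chosen, clinician and patient know only that the lesion is suspected to be T1. A proportion calculated among lesions that prove to be pT1 describes a group that cannot be identified at that moment. A reader who applies it to a patient with suspected T1 would overstate the chance of cancer cure by CAL-WR alone. A patient whose lesion proves to be pT2 has an indication for further surgery but is in neither the numerator nor the denominator.

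The listed secondary endpoints do not fill this gap. Technical success and radical resection are effectiveness measures, but a pT2 lesion removed with clear margins could count as a success on both and still carry an indication for completion surgery. The Abstract and Objectives also tie the R0 rate to T1.

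The primary figure also does not move with the accuracy of the expert panel, although the Discussion calls accurate inclusion the study's biggest challenge.

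**Working it through.** **Inputs**, all from Sample size calculation: expected proportion 45%; two-sided 95% interval of full width 0.2; pT2 15%; benign 10%; technical failure 10%; 96 pT1 patients; 143 in total; mid-term threshold of 60% for the pT1 share.

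**Reproducing the plan's figures**
- Wald precision formula: n = 4 × 1.96² × 0.45 × 0.55 / 0.2² = 95.08, rounded up to 96.
- Inflation: 96 / [(1 − 0.15 − 0.10) × (1 − 0.10)] = 96 / 0.675 = 142.2, rounded up to 143.

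Both match, so the working below uses this structure: technical failure first, then histology among completed procedures.

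**Expected patients among 143**
- Technical failure: 0.10 × 143 = 14.3, leaving 128.7 completed.
- pT2: 0.15 × 128.7 = 19.3.
- Benign: 0.10 × 128.7 = 12.9.
- pT1: 0.75 × 128.7 = 96.5 (plan: 96).
- pT1 low-risk and R0: 0.45 × 96 = 43.2. Other pT1: 0.55 × 96 = 52.8.

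**The same result on three denominators**

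| Quantity | pT1, completed (96) | Completed CAL-WR (128.7) | All included (143) |
|---|---|---|---|
| pT1 cured by CAL-WR only | 45% | 43.2/128.7 = 34% | 43.2/143 = 30% |
| Segment preserved, including benign | – | (43.2 + 12.9)/128.7 = 44% | 56.1/143 = 39% |
| Completion surgery indicated | 55% | (52.8 + 19.3)/128.7 = 56% | 72.1/143 = 50% |

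The 50% excludes the roughly 14 technical failures, whose further course is a separate matter. Of the 72 patients with an indication, about 53 are pT1 and can be read from the primary result. About 19 are pT2 (19.3/143 = 13% of those included) and cannot.

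**Sensitivity**
- How the exclusions combine: additive, 0.45 × 0.65 = 29.3%; fully multiplicative, 0.45 × 0.85 × 0.90 × 0.90 = 31.0%.
- Panel accuracy: with 45% and 10% technical failure held fixed, a pT1 share of 75% gives 0.75 × 0.90 × 0.45 = 30% of included patients. A share of 60% gives 0.60 × 0.90 × 0.45 = 24%. The primary figure is 45% in both cases.
- Precision: 43/143 has a Wilson 95% interval of 23.2% to 38.0%, about 15 points wide, against the planned 20 points for the primary endpoint.

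**Second operations: two descriptions side by side.** Follow-up lists three groups for whom completion surgery is advised. The cost paragraph names two and leaves out incompletely resected low-risk T1. A count based on the cost paragraph would therefore be smaller than one based on Follow-up.

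**The case against.** The strongest defence is that this is a declared choice. The pT1 denominator is the same in the Abstract, Objectives, Primary endpoint, Sample size calculation and Data analysis. It also fits the purpose of avoiding unnecessary segmental resection in low-risk T1: a pT2 lesion is arguably a selection miss and not a failure of the technique. That stands. A reader might infer that the plan contradicts itself or conceals the restriction; the documents support neither.

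A reader might also infer that the whole fall from 45% to 30% comes from conditioning on histology. It does not. Part of it is technical failure; among completed procedures the cure figure is about 34%. Segment preservation including benign lesions is about 44% of completed procedures, close to 45%, and the Abstract names organ preservation as part of the primary outcome. That also stands, and is a reason to show technical failures separately.

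Nor does the plan hide the second-operation burden. A 45% result tells the reader that 55% of pT1 patients were not cured by CAL-WR alone, close to the indication rate over everyone. The pT2 patients are grouped and managed under Follow-up, with quality of life measured in all patients. Data analysis compares patients with and without additional resection, and the cost analysis considers those needing two operations. What remains is narrower: that count serves a cost calculation, is not an outcome proportion with an interval, and has a definition that differs from Follow-up.

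It would also go too far to say that the trial cannot answer its aim. Safety, survival, costs and quality of life are listed without a pT1 restriction, and the mid-term check monitors the pT1 share. Further descriptive proportions may be in the full protocol or an analysis plan not shown here. The primary denominator and the endpoint list are fixed in this document, however, and the point concerns those.

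**Conclusion.** The point holds as a mismatch between the population in the aim and the population in the primary proportion. By itself, the pT1 figure does not give the success rate for patients in whom CAL-WR is chosen. On the planning assumptions, a 45% result corresponds to about 30% of included patients (29% to 31% depending on how the exclusions combine) or about 34% of completed procedures. Segment preservation is about 39% and 44% respectively. About half of included patients would have an indication for completion surgery, including about 19 pT2 patients outside the primary figure.

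These sizes assume that all 143 start CAL-WR, that technical failure is equally common across histologies, that the failures count as neither cured nor preserved, and that benign lesions removed successfully count as preserved. They follow from planning values and do not predict the result. The pT1 proportion remains valid as a conditional figure. The change should be made, but neither the primary endpoint nor the sample size is undermined.

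**What to change.** Keep the pT1 primary endpoint and the 143 patients. Add to Secondary endpoints and Data analysis the following named proportions, each with a 95% confidence interval, over all patients in whom CAL-WR was started:

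1. pT1 cured by CAL-WR only;
2. segment preserved, including benign lesions;
3. completion surgery indicated, and completion surgery received.

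Show technical failures as a separate line, so that their effect can be told apart from that of histology. Reconcile the cost paragraph's description of patients needing two operations with the groups listed under Follow-up, so that one definition is counted throughout. Word the primary result as conditional on the lesion proving to be pT1, and draw conclusions about primary treatment of suspected T1 from the new proportions.

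The cost is analysis and reporting text. Histology, margin status, technical success and additional resection are already needed for the planned analyses, and the expected interval of about 15 points calls for no extra patients. The downside is that a less favourable figure stands beside the headline.
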